#### Dietary advices

After the ESM assessment, the participant starts with either patient-tailored PROfeel lifestyle advices or generic dietary advices (see Table 1). The dietary advices are based on healthy and sustainable food-based dietary guidelines from the Netherlands Nutrition Centre (NNC), adjusted for age and gender [32]. The investigator provides the participant with information on the NNC dietary recommendations, including an overview of recommended foods and drinks available in local supermarkets. The general Dutch population is familiar with these guidelines as the “Wheel of Five”, a nutritional-counselling model that helps Dutch consumers make healthy food choices. In addition, participants fill out the “Eetscore”, an instrument developed to help consumers and health professionals improve their eating habits [33]. The instrument assesses the extent to which food and beverage intake conforms to the NNC’s dietary recommendations. The Eetscore provides 16 subscores, with higher scores indicating better adherence to the guidelines. The scores are presented as feedback to the participant, accompanied by educational background information on the guidelines and tips and tricks for incorporating the recommendations in daily life. Through the Eetscore tool, personal areas for dietary improvement are highlighted to the participant.

The participant adheres to the diet for 12 weeks. During these 12 weeks, the participant receives two weekly surveys. One survey requiring after the levels of fatigue, quality of life, and self-efficacy, and one survey requiring after the level of compliance to each dietary guideline. When participants respond non-adherence to a guideline, they will be asked to indicate whether they consumed more or less than recommended. This results in a weekly nutrition survey of 16 to 27 items.

### Criteria for discontinuing or modifying allocated interventions {11b}

This is a minimal risk study. Therefore, we have not specified criteria for discontinuing or modifying allocated interventions. Study participation is voluntary. Participants always have the right to withdraw from participation prematurely at any time, without providing an explanation. The investigator may also withdraw any participant who is unable to complete the QFS-study due to deteriorating health or another reason.

### Strategies to improve adherence to interventions {11c}

During the RCT, participants receive a boost from the investigator by phone and/or mail. Participants are also regularly reminded that they can contact the investigator for questions or help with their advice or technical problems with the app.

To improve adherence to the patient-tailored PROfeel lifestyle advices, the advices are formulated clearly and concretely (e.g., “cycle to school 3 days a week to increase physical activity” rather than “increase physical activity”). This way, participants know what is expected of them. Participants receive a weekly survey item on their smartphone, inquiring after their level of compliance.

To improve adherence to the generic dietary advice, participants receive a weekly survey inquiring after their compliance to each aspect of the dietary advice. The surveys function as both monitoring and reminder tools for the participant. Reminders are often used as a tool in behavior change interventions [30], and a meta-analysis has shown that reminders can make a small contribution to behavior change in dietary interventions [34].

### Relevant concomitant care permitted or prohibited during the trial {11d}

Participants are ineligible if they already participate in a behavioral intervention aimed at reducing fatigue severity. However, it is allowed to receive concomitant care focused at reducing fatigue severity if this is part of the patient-tailored PROfeel lifestyle advice (e.g., physiotherapy directed at body mentalization). It is also allowed to receive concomitant medical or psychological care, if this was already started before the intervention and as long as the primary focus of this treatment is not directed at reducing the fatigue.

### Provisions for post-trial care {30}

Before enrollment in the RCT, all fatigued participants will receive oral and written information of optional post-trial care at the Dutch Expert Centre for Chronic Fatigue (ECCF). Regular care, such as CBT will be offered following the study without waiting list. If desired, the participant decides in consultation with the therapist whether this treatment will be followed additionally.

### Outcomes {12}

Primary outcome of the intervention study is “fatigue severity”. Secondary outcomes are “self-efficacy” and “quality of life”. All outcomes are measured at study visits T0–T4 and through weekly measurement by smartphone (see Table 1). For details on outcome measurement, see section “Plans for assessment and collection of outcomes” {SPIRIT Item 18a}. For information on the biological study outcomes and laboratory evaluations, see section “Plans for collection, laboratory evaluation, and storage of biological specimens for genetic or molecular analysis in this trial/future use” {SPIRIT Item 33}.

### Participant timeline {13}

Participant timeline is shown in Table 1.

### Sample size {14}

As described earlier, the QFS-study concerns a RCT with implemented *N*=1 design. The objectives of the study with *N*=1 design do not require a sample size calculation. Therefore, power analysis was performed for the group-level analyses on the primary outcome “fatigue severity”, which will be measured pre-post interventions. Based on previous CBT studies aiming to reduce chronic fatigue [18, 26], with an alpha of .05, power of .80, repeated measures correlation of .23, and an anticipated Cohen’s *f* effect size of .5, the sample size calculation for repeated measures 2 × 2 ANOVA yields *n*=16 per group. Taking into consideration an expected drop-out rate of 20% from previous single-subject experimental case research with multiple measurement on severe fatigue in adolescent patients with an immune dysregulation disorder, we will include 20 participants per group (i.e., QFS, CFS/ME, JIA), resulting in *N*=60. With *N*=60, it was decided upon expert medical and research lab opinion to include up to 80 healthy controls to increase the likelihood of recruiting healthy controls with seropositive *Coxiella burnetii* status, of observing contrasts in biological parameters, and to enable matching for age and gender as much as possible.

### Recruitment {15}

Adolescents and young adults with QFS and long-COVID will be notified through respectively the Q-support network and C-support network, as well as through notifications on the UMC Utrecht and University of Utrecht (UU) website. Adolescents with CFS/ME and JIA are regularly seen at the outpatient clinics by general pediatricians and pediatric immunologist/rheumatologists at UMC Utrecht and made aware of the study through them. After a uniform diagnostic work-up (via medical history, laboratory examinations, and questionnaires) done by the social pediatrician and pediatric immunologist/rheumatologists, patients and their parents receive detailed oral and written information about the QFS-study from the investigator. Information about the study has been approved by the Institutional Review Board (IRB) of UMC Utrecht (reference NL72103.41.20, IRB 20/166). Ultimately, all adolescents and young adults complying with the defined inclusion criteria will be invited for this study.

## Assignment of interventions: allocation

### Sequence generation {16a}

Fatigued participants will be randomized to their first intervention, which is either patient-tailored PROfeel lifestyle advices or generic dietary advice, in a 1:1 ratio. Computer-generated concealed block randomization will be used. Randomization will be stratified by group (i.e., QFS, CFS/ME, and JIA) to distribute participants equally across the intervention arms.

### Concealment mechanism {16b}

Concealment will be accomplished electronically. Only one independent statistician has access to the randomization outcome. In case the participant will be assigned to the patient-tailored PROfeel lifestyle condition, it is necessary for the investigator to know this in advance in order to prepare the PROfeel report. Therefore, the investigator contacts the statistician by email to inquire about the allocation for that participant, three working days before the second study visit (i.e., T1).

### Implementation {16c}

The allocation sequence was generated in SPSS by the independent statistician on the research team and he is the only one with access to the randomization outcome. The investigator is responsible for contacting the statistician three working days before the second study visit (T1) to inquire allocation. The statistician responds by email. In all correspondence, the investigator and statistician use pseudonymized codes to refer to participants (e.g., “QFS-1”, CFS-3”, and “JIA-20”).

## Assignment of interventions: blinding

### Who will be blinded {17a}

The analyses of the ESM data will be conducted by the independent statistician, who has no contact with the participants. In order for the statistician to interpret the ESM data without prior knowledge of the participant, the investigator will only refer to participants using an anonymous code (e.g., “QFS-1”, “CFS-3”, and “JIA-20”). When the statistician reveals the assignment to the first condition, the investigator will share this with the participant during study visit T1.

All biological samples (i.e., blood, stool, saliva, hair) will be labelled with the participant’s study number without any reference to diagnosis (i.e., 1, 2, … 140). Only the investigator has an overview of which study number matches which participant. The investigator is responsible for matching healthy controls to fatigued participants as much as possible, based on age and gender. The investigator is not present during lab analyses.

### Procedure for unblinding if needed {17b}

No procedures are needed for unblinding.

## Data collection and management

### Plans for assessment and collection of outcomes {18a}

The primary outcome of the intervention study is “fatigue severity” as measured by the subscale “fatigue severity” (8 items) of the Checklist Individual Strength-20 (CIS-20). The subscale consists of 8 items (CIS-8). Participants will receive the CIS-8 once a week throughout the study as a survey in the Ethica smartphone app. The weekly CIS-8 has a scoring range of 8–56, with higher scores indicating more fatigue. The CIS-8 has good reliability and discriminative validity [35]. A reduction of 1 standard deviation (SD) is considered clinically relevant.

Secondary outcomes of the intervention study are “quality of life” and “self-efficacy”. Per construct, one VAS item will be added to the weekly CIS-8 questionnaire. In addition, these outcomes will be measured with questionnaires in KLIK, a web-based survey portal (www.hetklikt.nu). “Quality of life” will be measured with the Pediatric Quality of Life Inventory 4.0 Generic Score (PedsQL GCS). This questionnaire consists of four subscales (i.e., physical, emotional, social, and school or work functioning), with total- and subscores ranging from 0 to 100. Higher scores indicate a higher quality of life. The PedsQL GCS has good validity and reliability [36]. An increase of 1 SD is considered clinically relevant. “Self-efficacy” is defined as a sense of control over fatigue symptoms and will be measured with the Self-Efficacy Scale-28 (SES-28). This questionnaire consists of 5 items that inquire about the sense of control related to fatigue, with higher scores indicating more sense of control [37]. An increase of 1 SD will be considered clinically relevant.

With KLIK, we also measure possible predictors, mediators, or moderators of the primary outcome “fatigue severity”. The choice of measurements was guided by whether the following aspects could be predictive for the effectiveness of the interventions. The outcomes are: “fatigue severity at baseline” measured with the CIS-8 questionnaire [26], “quality of life at baseline” measured with the PedsQL GCS [36], “self-efficacy at baseline” measured with the SES-28 [35], “sleep problems” measured with the PedsQL Multidimensional Fatigue Scale (PedsQL MFS) [36], “daily participation” measured by school or work presence expressed in hours attended divided by hours obliged multiplied by 100, “pain level” measured using a visual analogue scale (VAS) to indicate average pain over the last week, and “depression or anxiety symptoms” measured with the Revised Child Anxiety and Depression Scale (RCADS) [38].

KLIK measurements are completed at baseline (T0), pre-intervention (T1 and T3), and post-intervention (T2 and T4). See also the participant timeline in Table 1.

With the Eetscore tool, we measure dietary intake pre- and post-dietary intervention. The outcome is the total difference score, which reflects the amount of change in dietary intake as a result of the dietary intervention. The Eetscore is typically used for assessing dietary intake in people aged 18 years or older [33]. For the QFS-study, the University of Wageningen adjusted the Eetscore to make it usable for people aged 12 years and older. To enable validation of the adjustments, participants below the age of 18 will be given the option to also complete the validated Food Frequency Questionnaire (FFQ) [39].

Regarding the biological outcomes and laboratory evaluations, see section “Plans for collection, laboratory evaluation, and storage of biological specimens for genetic or molecular analysis in this trial/future use {33}”.

### Plans to promote participant retention and complete follow-up {18b}

The QFS-study will use multiple strategies to promote that participants do not drop out of the study and complete follow-up. For example, we will minimize the burden of assessments, send reminder letters, emails, or phone calls, provide patients with study team contact information, and combine study visits with usual care visits whenever possible. Study visits will be scheduled as flexible as possible. To enable intention-to-treat analyses, participants who withdraw prematurely from the QFS-study will be encouraged to complete follow-up assessments. Participants’ reasons for withdrawing will be recorded whenever possible.

### Data management {19}

Collected data will be stored by the Wilhelmina Children’s Hospital of UMC Utrecht for 15 years following completion of the project. A Data Management Plan (DMP) has been prepared and evaluated by the UMC Utrecht’s data quality management team. It applies FAIR (Findable, Accessible, Interoperable, Reusable) principles to the QFS-study data.

### Confidentiality {27}

Data will be handled confidentially according to the rules of General Data Protection Regulation (GDPR). Only researchers directly involved in the project will have access to the codes and participant data, which will only be stored in password-protected files. However, in case participants decide to follow post-trial care at the ECCF, the treating therapist at the ECCF will receive the baseline assessment and PROfeel data required to indicate which treatment modules should be provided. Computers used to access the data will be protected in accordance with UMC Utrecht standards. Paper forms (e.g., informed consent from participants, parents or legal guardians, and investigator notes from PROfeel conversations) will be stored in a locked file cabinet at the Wilhelmina Children’s Hospital.

### Plans for collection, laboratory evaluation, and storage of biological specimens for genetic or molecular analysis in this trial/future use {33}

In the QFS-study, biological samples will be collected from participants at study visits T1, T2, and T4 (see Table 1). Healthy controls will have only one study visit, during which the same biological samples will be collected (i.e., blood, stool, saliva, and hair). All biological samples will be stored and saved at the UMC Utrecht biobank for 15 years.

The T1 samples will be used to explore the biological profile and to identify disrupted biological factors in fatigued participants (objective 4). Participants will be matched to healthy controls, based on age and gender. Blood samples will be used to (1) determine the sensitivity of the immune system to regulation by glucocorticoids in participants compared to Q-fever seropositive and Q-fever seronegative healthy and controls; (2) assess the sensitivity to adrenergic regulation of the immune system in QFS, CFS/ME, and fatigued JIA participants compared to respective healthy controls and; (3) to assess metabolic dysfunction by means of image stream, flow cytometric analyses of superoxide production, unbiased metabolomics analyses to assess the downstream consequences on the metabolome, and unbiased transcriptional analyses. Due to the technical complexity, costs and time consumption of these assessments, metabolic dysfunction, and transcriptional analyses will be assessed for QFS and CFS/ME participants and matched healthy controls.

Hair samples will be used to evaluate cortisol and possibly cortisone levels in QFS, CFS/ME, and fatigued JIA participants and healthy controls. Stool and saliva samples will be collected for microbiome analyses in QFS, CFS/ME, and fatigued JIA participants and healthy controls. The microbiome data will be linked to clinical and patient-reported outcomes to investigate whether we can discriminate between subgroups of chronic fatigue, and to identify which operational taxonomic units are relevant for distinction between the disease groups.16sRNA sequencing will be applied to measure bacterial composition at the genus (possibly species) level. Using this 16s phylogenic profiling method, it is possible to get an overview of the community composition of a bacteria and identify differences between groups and variation within groups. DNA extraction, library preparation, sequencing, and basic annotation will be performed. For library construction and 16S rRNA gene sequencing, DNA extraction will be performed with the QIAamp DNA Stool Mini Kit.

The T2 and T4 samples can ultimately be used for objective 5, in which the relationship between individual improvement differences in “fatigue severity” and subsequent changes in biological profiles will be explored.

## Statistical methods

### Statistical methods for primary and secondary outcomes {20a}

To evaluate on the group level the effectiveness of the patient-tailored PROfeel lifestyle advices against generic dietary advices in reducing “fatigue severity” and improving “quality of life” and “self-efficacy” (objective 1), two statistical tests will be performed. The first test, is a 2 × 2 ANCOVA with “fatigue severity” at T2 as dependent variable, “fatigue severity” at baseline as covariate, and intervention condition as fixed factor. This test is used to compare the reduction in “fatigue severity” for the PROfeel-first group against the dietary-first group. The second test is a repeated measures 2 × 2 ANOVA to test whether the order in which participants received the advices is of relevance. The same tests will be performed for secondary outcomes “quality of life” and “self-efficacy”.

To evaluate the effectiveness of the patient-tailored PROfeel lifestyle advices and generic dietary advices in reducing “fatigue severity” and improving “quality of life” and “self-efficacy” at the individual level (objective 2), the permutation distancing test (PDT) will be used. This test is currently under development (see supplement of 41). This test takes into account autocorrelation, handles missing data by making optimal use of all observations, and is specifically developed for *N*=1 designs with a fixed intervention start.

To explore individual effects on pre-post intervention change in the dynamic networks for the participants who first receive patient-tailored PROfeel lifestyle advices first (objective 3), single-subject residual dynamic structural equation modelling (RDSEM) [40] will be used in Mplus. We will model the pre- and post-intervention dynamic networks in one SEM model [41]. This allows for statistical testing of the differences between the pre- and post-network estimates.

To explore the biological profile of adolescents and young adults with QFS and compare it with participants with CFS/ME and JIA, as well as healthy controls (objective 4), we will use between-group ANOVAs and/or linear regression analyses.

Exploration of the relationship between individual differences in “fatigue severity” improvement and biological profile changes pre-post interventions (objective 5) will be conducted with growth mixture modelling (GMM) [42] in Mplus.

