#### Additional criteria for participants with JIA

All 20 participants must enter the screening process with a diagnosis of JIA. Participants must be on stable medication and have a stable disease activity score (Juvenile Arthritis Disease Activity Score; JADAS criteria) [27] for at least 3 months. Participants cannot have a QFS diagnosis. At the time of screening, the participant must express fatigue as a main complaint in the last 3 months. At the time of screening, fatigue must be severe (i.e., CIS-8 > 34, which indicates severe fatigue in JIA).

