### Methods for additional analyses (e.g., subgroup analyses) {20b}

Not applicable, no additional analyses will be conducted.

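### Randomisation is stratified by diagnosis, but the group-level ANCOVA omits diagnosis; this costs precision if diagnosis predicts T2 fatigue beyond baseline

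*Protocol article*

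**What the plan says.** Sequence generation {16a} gives a 1:1 ratio and states: "Computer-generated concealed block randomization will be used". It continues: "Randomization will be stratified by group (i.e., QFS, CFS/ME, and JIA) to distribute participants equally across the intervention arms". Diagnosis is the only stratification factor named.

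Statistical methods for primary and secondary outcomes {20a} describes two group-level tests. The first is called a 2 × 2 ANCOVA. Its dependent variable is fatigue severity at T2, with fatigue severity "at baseline as covariate, and intervention condition as fixed factor", and it compares the reduction in fatigue "for the PROfeel-first group against the dietary-first group". The second is a repeated-measures 2 × 2 ANOVA for the order of the interventions. Both are repeated for quality of life and self-efficacy. Neither description mentions diagnosis.

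The section on additional analyses {20b} reads: "Not applicable, no additional analyses will be conducted". No other section brings diagnosis into the effectiveness comparison.

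**The concern.** Blocking within diagnosis keeps the arms balanced on diagnosis, so differences between diagnoses largely cancel out of the arm comparison. A model without diagnosis still counts those differences as residual noise. Its standard error then describes a less precise design than the one that was run. The confidence interval is wider than it should be, and the test rejects less often than its nominal level.

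This happens only if diagnosis carries information about T2 fatigue that baseline fatigue does not. The article gives reasons to think it may:

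- **Entry threshold.** The JIA criterion is "CIS-8 > 34, which indicates severe fatigue in JIA", whereas QFS and CFS/ME enter above 39.
- **Disease stability.** JIA participants must also have had stable medication and disease activity for at least 3 months.
- **Age.** The Discussion expects QFS participants to be older than most of the others.

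The 2 × 2 label adds doubt about the model. One two-level factor and a covariate do not make a 2 × 2 layout, and a three-level diagnosis factor could not supply the second 2.

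**Working it through.** **Inputs from the article.** Sample size {14} plans "with an alpha of .05, power of .80, repeated measures correlation of .23", Cohen's f of .5, 16 per diagnosis group, 20% dropout, and 20 per diagnosis group (60 in total). The ANCOVA terms are those in {20a}.

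**Assumed inputs.** R² is the share of the baseline-adjusted residual variance explained by diagnosis. The documents give no value, so the range 0 to 0.30 is used. A difference of 0.6 SD is used as a second effect size; it is not in the documents.

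**Step 1: the plan's own figure.** For the within-between interaction with two arms and two times, λ = f²·N·m/(1 − ρ), with df 1 and N − 2.

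- N = 16: λ = 0.25 × 16 × 2 / 0.77 = 10.39, power 0.850.
- N = 14: λ = 9.09, power 0.790.

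The smallest even N that reaches 0.80 is 16, as stated. Then 16/(1 − 0.2) = 20 and 3 × 20 = 60. Completers number 60 × 0.8 = 48, or 24 per arm.

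**Step 2: standard error.** Set the residual variance after baseline adjustment to 1.

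- Reported SE without diagnosis: √(2/24) = 0.289.
- True SE with balance inside diagnoses: √((1 − R²) × 2/24).
- Ratio: 1/√(1 − R²). At R² = 0.20 this is 0.289/0.258 = 1.118.

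**Step 3: type I error and power.** Without diagnosis, df = 48 − 3 = 45 and the two-sided 5% critical value is in effect multiplied by the ratio from Step 2. With diagnosis, df = 48 − 5 = 43 and the usual critical value applies. Power uses the noncentral t with noncentrality d divided by the true SE. The f of .5 is read as d = 2f = 1.0 for two equal arms.

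| R² | SE ratio | Type I error, diagnosis omitted | Power at 0.6 SD, omitted → included | Power at d = 1.0, omitted → included |
|---|---|---|---|---|
| 0 | 1.000 | 5.0% | 53.0 → 52.9% | 92.4 → 92.3% |
| 0.05 | 1.026 | 4.5% | 53.0 → 55.0% | 92.9 → 93.5% |
| 0.10 | 1.054 | 3.9% | 53.1 → 57.2% | 93.4 → 94.6% |
| 0.20 | 1.118 | 2.9% | 53.3 → 62.2% | 94.4 → 96.6% |
| 0.30 | 1.195 | 2.0% | 53.5 → 68.0% | 95.5 → 98.2% |

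The effect is in units of the residual SD. If 0.6 is instead read in raw T2 SDs with the planned correlation, the residual variance is 1 − 0.23² = 0.947. Power then goes from about 55% to about 60, 65 and 70% at R² of 0.10, 0.20 and 0.30. The gain is much the same.

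**Step 4: simulation.** With all 60 participants and R² = 0.20, the model without diagnosis reported a mean SE of 0.260. The actual SD of the estimate was about 0.233 (ratio 1.12), and type I error was 2.9%. At R² = 0 the two models agreed.

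**Step 5: unbalanced completers.** Steps 2 and 3 assume 8 completers per arm in each diagnosis. Starting from 10 per arm per diagnosis with random 20% dropout, the SE overstatement falls to about 4–5%, 8% and 13–15% at R² of 0.10, 0.20 and 0.30. Type I error is then about 4.0%, 3.4% and 2.5%.

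**The case against.** The strongest counter-argument is that the loss is conditional and may be small.

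- **Premise.** The Background treats fatigue as a generic symptom across diseases, which argues against a large diagnosis effect. This stands as a reason to keep R² of 0 to 0.05 in the range.
- **Entry thresholds.** They are a difference in baseline CIS-8, and baseline is already the covariate. This stands in part. At the planned correlation of .23, baseline explains only 0.23² ≈ 5% of T2 variance, so it may absorb little of a lasting difference between diagnoses. Whether such a difference exists is unknown.
- **Upper end of the range.** Suppose only JIA differs, by δ within-group SDs, in three equal groups. Then R² = (2δ²/9)/(1 + 2δ²/9). R² of 0.10, 0.20 and 0.30 needs δ of 0.71, 1.06 and 1.39. The protocol treats 1 SD as a clinically relevant change, so the top values assume a large leftover difference. This stands.
- **Planned effect.** At d = 1.0 power is above 92% either way. This stands for power, although the interval would still be too wide. The f of .5 comes from earlier CBT studies, whereas this trial compares two advices and expects the diet itself may reduce fatigue. A smaller difference between arms is therefore possible.
- **Left to the SAP.** A condensed article may leave covariate lists to a fuller document. That does not answer the point, because {20a} names the dependent variable, covariate and factor, and the model so named omits the stratifier.

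A reader might infer that the arm comparison is biased or that false positives become more likely. Neither follows: the estimate is unbiased and type I error stays at or below 5%. A reader might also infer that the standard error is certainly too large or that the trial is thereby underpowered. The documents give no figure that would establish either.

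**Conclusion.** The mismatch is real: the stratification factor is missing from a model whose terms are stated, and the 2 × 2 label does not describe that model. Its consequence is a possible loss of precision, conditional on diagnosis predicting T2 fatigue beyond baseline. The loss is negligible at R² of 0.05 or less. At R² of 0.10 to 0.30 the standard error is overstated by about 5 to 20% with balanced completers, and by about 4 to 15% with random dropout. In power this is worth up to about 15 points at 0.6 SD and up to about 3 points at d = 1.0. The R² values and the 0.6 SD are assumptions, and d = 1.0 is a reading of the protocol's f. The change is worth making because it is nearly free; the validity of the trial does not depend on it.

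**What to change.** Specify the first group-level test as an ANCOVA of the T2 outcome on arm, the baseline value of that outcome and diagnosis (QFS, CFS/ME, JIA). Use this form for fatigue severity, quality of life and self-efficacy. Drop the 2 × 2 label, or explain what the second factor is.

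In the repeated-measures order test, include both diagnosis and diagnosis by time. A diagnosis main effect alone does not sharpen within-person contrasts.

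The cost is a line or two of analysis wording and, in the ANCOVA, two degrees of freedom (45 to 43 with 48 completers). If diagnosis turns out not to be prognostic, that costs about 0.1 power point.
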